**Block 1 or initial block.**

It consists of two sessions:

S0 In the first session, parents and adolescents will be informed about the procedure of the experiment and asked for cooperation. Those who agree to participate must sign the Informed Consent document. In this session, participants fulfilling the inclusion criteria will undergo the first psychological assessment consisting of the following tests:CACIA [32]. This questionnaire evaluates self-control by means of four scales: three positive (Personal Feedback, Reward Delay and Criterial Self-Control) and one negative (Processual Self-Control). It also incorporates a Sincerity scale. Its scales focus on the evaluation of Self-Control considered from a behavioral point of view, whose basis is the conscious effort of the person to modify his or her reactions.STROOP test [33]. This reference test is employed in the detection of neuropsychological problems and brain damage. It allows evaluating the phenomenon of interference, which is strongly linked to inhibitory control processes.Wisconsin Card Sorting Test (WCST) [34]. This test assesses the ability required to develop and maintain the problem-solving strategies necessary to achieve a goal. It is particularly sensitive to lesions involving the frontal lobes (Stuss *et al*., 2000), thus it is very useful for discriminating between frontal and non-frontal lesions.The Child Behavior Checklist (CBCL) [35] is a standardized assessment tool used to identify emotional and behavioral problems in children and adolescents. Parents or caregivers, in addition to the children themselves (Youth Self Report (YSR)), complete the checklist by rating their behavior, providing valuable insights into various domains such as anxiety, depression, and aggressive behavior. The CBCL and the YSR are part of the Achenbach System of Empirically Based Assessment (ASEBA), which is widely used in both clinical and research settings to inform diagnosis and treatment planning.
S1 Families will be the active part of the experiment in the second session, which takes place at home, not at the research center. A small camera will be hidden in the living room, while the adolescents wear a wristband that records multiple biosignals (HR, SCL and skin temperature (ST)). The goal is to register the scene together with physiological variables before, during and after at least up to four aggressive outbursts.The experimenter will synchronize both the camera and the wristband, and instruct parents to extract the physiological information, make the video clip containing the aggressive episodes, and annotate when they started.

**Block 2.**

The second block consists of a recording session at the laboratory, which is repeated three times.

S2–S4 In these sessions, parents, scientists, adolescents and psychologists will meet to try and reproduce the outburst and record physiological signals before, during and after the aggressive episode.These sessions contain several phases:**Baseline register.** Initially, the researchers will set up the system and start recording a baseline reference for approximately 5 minutes [36].**Relaxation.** After the baseline register phase, adolescents will move on a relaxation phase, in which they will use an immersive Virtual reality (VR) system for 10 minutes. In this phase, participants can move into a landscape while listening to ambient sounds (birds and sea waves). VR, particularly immersive virtual reality (IVR), has demonstrated its effectiveness in therapy with people with behavioral disorders, improving emotion recognition, social skills, and attention, while diminishing their anxiety and phobias [37–39].**Evoking an outburst.** In the following phase, adolescents will watch the recorded aggressive outburst while their parents explain to the therapist the reasons that caused such an episode, including all the necessary details that favor the elicitation of a new outburst. Different videos will be used in each session to avoid the accommodation effect. Re-experiencing a situation that previously triggered an anger outburst can indeed provoke it again. This is because recalling emotionally charged events can activate the same brain areas involved in the original emotional experience [40]. According to the classical conditional model, if a particular situation has been previously associated with an anger response, re-exposure to that situation can trigger anger again due to conditioned memory [41].**Relaxation.** At the end of the episode, parents will leave the room for a while, and the participants will go to a new relaxation phase for another 10-minute period using again the VR.

Fig 2 depicts the phases and actions in this important session. The experimenter will tag the beginning of each phase in this session and will mark the moment when the impulsive outburst appears. By doing so, researchers will be able to analyze offline how the physiological information changed and how it can be included in the therapy. There will be a digital diary to collect tests outcomes and any relevant information regarding the patient during the session, including whether the outburst was evoked successfully. Data will be discarded from analysis when it is not possible to evoke the outburst.

The data collected in this block will allow assessing the influence of an aggressive episode on physiological signals. This will be used to teach individuals to identify when an outburst is about to occur, and prevent it.

**Block 3.**

S5 Only for the intervention group. The adolescents will be trained to identify the physiological response when they are relaxed and when an outburst is coming. It is possible to use these responses to predict the aggressive outburst at least one minute before it manifests [42]. To do this end, the VR system receives and shows HR, HRV, and SCL on the virtual scenario. Therapists will help participants identify the physiological features related to aggressive outburst based on the data collected in previous sessions (Block 2).S6–S9 They are similar in both intervention and control groups, and follow the same layout as the sessions in block 2, excluding the last phase:**Cognitive therapy in the control group.** After evoking an outburst, adolescents will be trained with cognitive, behavioral and emotional self-regulation therapies [43], which have proven their effectiveness for managing anger and learning positive coping skills. The underlying theory is that people can minimize their negative feelings and behaviors when they are aware of their irrational beliefs and work to change their minds, by focusing on them continuously. With this therapy, people are endowed with strategies to improve their capabilities of identifying negative thoughts and beliefs in situations of conflict and/or frustration, which are the main triggers of aggressive outbursts. The goal is to ensure that, through identifying such thoughts and becoming more aware of their emotions, the individual gradually dismantles those irrational thoughts.**Cognitive therapy in the intervention group.** Participants will follow the same cognitive therapy as the controls, although they will receive information through biofeedback. By identifying this information and applying the skills learned in therapy, participants are expected to better manage or avoid imminent outbursts.

At the end of session S9, the CACIA, Stroop, CBCL, YSR and WCST tests will be assessed again. The differences between the new obtained physcological scores, with respect to the initial scores, along with the differences between control and intervention groups, will be used to assess the efficacy of the intervention.

### Materials

**Wifi camera.** A camera (model Tapo C200), which captures video and audio, will be hidden in the living room, which captures an aggressive outburst. The experimenter will synchronize this camera to the Empatica E4 wristband.

**Empatica embrace plus.** Adolescents will have to wear this wristband for several days at home. It records multiple biosignals (photoplethysmogram (PPG) [44], electrodermal activity (EDA) and skin temperature (ST)) at a sampling rate of 64Hz. Heart rate (HR) and heart rate variability (HRV) can be extracted from photoplethysmogram (PPG) and electrodermal activity (EDA) allows estimating the SCL. The camera will be synchronized to the wristband using their own internal clocks.

**Physiological recording system.** For the sake or reproducibility of the laboratory sessions, several devices, not mutually exclusive, can be used to capture subject’s biosignals. Some of them are shown below:

**AAI Wearables.** The wearable devices described in [45] capture EDA and electrocardiog-raphy (ECG) and transmit raw data through Bluetooth low energy to a laptop that converts the incoming data into LSL streams. LSL (Lab-Streaming Layer) is a C++ library that allows data synchronization from multiple sources [46].

**Emotibit.** Emotibit records the same physiological signals as Empatica E4 [47]. It is less compact but more affordable. It also allows real-time signal transmission, although its battery life is more limited. As in the case of Empatica, Emotibit will be placed at the wristband during the laboratory sessions. An application called Emotibit Oscilloscope, running on a laptop, can receive, through WiFi connection, data from the Emotibit wristband, and then redirect the physiological signals to LSL streams on the computer network.

**Psychobit** BITalino PsychoBIT [48] is a pre-assembled device designed for basic psychophysiological data acquisition. It facilitates the measurement of various physiological signals, including pulse, blood pressure, respiration, and skin conductivity. The core of PsychoBIT is BITalino (r)evolution Plugged, which offers Bluetooth communication for seamless data transmission. The kit comprises several pre-assembled sensors: ECG, EDA, PPG, etc. Data are received by OpenSignals, which is a free software that allows redirecting raw or processed information, such as HR, which is obtained from ECG or PPG, to LSL streams.

Fig 3 shows a possible schematic based on EmotiBit.

**Fig 3 pone.0327361.g003:**
[figure not shown]
Experimental setup at the clinical setting. On the left, the person with the Emotibit for measuring physiological signals that are transmitted to the laptop. The subject also wears the VR glasses controlled by another computer that also receives physiological signals for biofeedback purposes.

**Recorder.** The laptop also hosts the LSLRec [49], which is based on Lab-Streaming Layer https://github.com/sccn/labstreaminglayer, a C++ library that allows data synchronization. LSLRec is an easy-to-use, open-source, multi-platform, recording system developed on Java. LSLRec reads data from LSL streams and stores them while maintaining synchronization with the experimental blocks and phases of the experiment.

**Virtual reality (VR) platform.** For the immersive VR we use the Meta Quest 3 headset, although any other commercial model of the same manufacturer could be used. The use of this device is allowed for the range of ages of the participants. The program has been developed using Unreal Engine, which is one of the most powerful real-time 3D creation tools, running on a personal computer that features a CPU AMD Ryzen 9 3950X, with a GPU model NVIDIA GeForce RTX 3070 and a X570 AORUS ULTRA motherboard with 64 GB RAM. The computer is connected to a local network in order to receive LSL streams [46] that contain the physiological information to show on the screen.

Fig 4 shows the two scenarios included in the VR for the relaxation phase. Participants can navigate through those scenarios using only one controller, which can be configured for left- or right-handed people. In the figures biofeedback information is also shown including HR, HRV and SCL.

**Fig 4 pone.0327361.g004:**
[figure not shown]
VR scenario. One of the VR scenes showing some physiological variables for biofeedback.

### Metrics

As a general procedure, outliers will be identified by applying the interquartile range method. We will then examine each outlier assess whether it could be attributed to measurements errors, technical issues, or specific characteristics of the participant. Data points will be excluded only when a clear justification exist (e.g: confirmed recording errors).

Continuous variables will be summarized using the mean and standard deviation (SD) when data are normally distributed. For variables that do not meet the normality assumption, we will report the median and interquartile range (IQR). Normality will be assessed through the Shapiro–Wilk test. Appropriate statistical tests (parametric or non-parametric) will be selected accordingly to the distribution of residuals.

**Psychological assessment.** Scores will be obtained by CACIA, STROOP, WCST, CBCL, and YSR tests at the beginning and at the end of the experiment. These tests contain 40 variables that will help assess the effect of the therapy and look into the underlying cognitive mechanisms regarding aggression, such as executive functions and other emotional or behavioral issues associated with it.

At the end of this section reader will find a list of the primary variables that directly measure the impact of the therapy and reflect key aspects related to self-regulation/-control, which are important to mitigate outbursts.

**Cardiac features.** One important feature, from which others can be derived, is instantaneous heart rate (HR). Both Empatica and Emotibit obtain HR from PPG signals by determining the position of their maximums and then calculating the time difference between two consecutive maximums.

Derived from HR, heart rate variability (HRV) in time analysis can be extracted from 2-minute windows by obtaining the root medium square (RMSSD) between maximums of the PPG peaks. The length of the windows will be selected to fulfill the requirements of frequency band analysis of the heart rate variability (HRV) spectrum [50].

HRV is especially interesting as it allows assessing the activity of the parasympathetic and sympathetic pathways of the autonomic nervous system (ANS) [51]. For instance, the ratio between low frequency, [0.04–0.15] Hz (LF) and high frequency, [0.15–0.4] Hz (HF), which is called the ratio between LF and HF (LF/HF), shows the balance between the SNS and the PNS.

HR and HRV will be used for biofeedback, although a much richer feature set will also be included for offline analysis [52].

**Skin conductance level (SCL) measurements.** The variation of the electrical conductance is referred to as EDA which is primarily due to sweat gland secretion. This activity is closely linked to the sympathetic nervous system, which is responsible for the body’s “fight or flight” response and therefore used as an indicator of physiological arousal, emotional responses, and stress. The two main components derived from EDA are skin conductance response (SCR) and skin conductance level (SCL).

SCL is the parameter that will be included in biofeedback and represents the baseline level of skin conductance over time, linked to emotional arousal.

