**Methods::**

A total of 70 participants will be recruited for a randomized controlled trial (RCT). All participants will receive therapy, although only the intervention group will incorporate biofeedback. The experimental study will be split into three blocks: (1) *Home Monitoring*: Physiological signals will be recorded using a smartwatch, and aggressive episodes will be captured with a camera; (2) *Laboratory Assessment*: Participants will attend three sessions, where therapists will induce aggressive reactions, using the video clips recorded at home. Simultaneously, real-time physiological signals will be measured. These sessions will also include relaxation periods before and after the provoked outburst; (3) *Therapeutic Intervention:* Similar to the laboratory assessment block, therapists will induce aggressive responses in three sessions; however, in this block, participants will receive therapy. Additionally, participants who belong to the intervention group, will include biofeedack in the therapy. Biofeedback is focused on heart rate (HR), heart rate variability (HRV), and skin conductance level (SCL). The CACIA, the Stroop, and other pre- and post-experimental tests. will be used to assess the differences between the control and intervention groups.

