## Materials and methods

### Participants

As explained above, the early onset of aggressive behavior is linked to higher biological risks and often leads to persistent antisocial behavior, highlighting the importance of applying treatment at early age. For this reason, the group to be studied will consist of 70 participants aged 10–16 years. They will be recruited from the INEBIR clinic, where the experimental sessions will be carried out, and other participants will be recruited from the Instituto Hispalense de Pediatría. The sample size was by analyzing the differences of the means according to a Student’s t with a confidence level of α=0.05, a test power of 1−β = 0.8 and a moderate effect size [30]. A moderate effect size (Cohen’s d = 0.5) represents a practically meaningful difference in the context of clinical decision-making, even if smaller effects may also be statistically detectable in larger samples and it is a commonly used convention in behavioral and clinical research when planning exploratory studies [31]. A moderate effect size results in 62 participants. For a small effect size (Cohen’s d = 0.2), we would need to recruit more than 300 participants, and we do not have the human and material resources to complete this study in a relatively short time. Additionally, to account for potential non-response or dropout, we included an additional 10%, bringing the final target sample size to 70 participants. This approach ensures sufficient power to detect differences between groups while anticipating common challenges in recruitment and retention.

To participate in this study, the following inclusion criteria will be applied:

Adolescents aged 10 to 16 whose parents seek professional help because their son or daughter exhibits aggressive outbursts that they are unable to manage.Intermittent aggressive episodes with a frequency of at least once a week in the two months prior to the start of the intervention.Not presenting some of the following:History of bipolar or psychotic disorder.Head trauma with loss of consciousness for more than 60 minutes.

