#### Assessment of cognitive therapy with biofeedback.

The main goal of this study is to verify the efficacy of the proposed therapy. At the beginning adolescents will fill in the CACIA, Stroop, WCST and CBCL tests. At the end of the therapy, these metrics will be assessed once more to compute the difference with the initial tests. These differences will be compared between the intervention and control groups to ascertain statistical significance. To this end, we will use the Mann-Whitney-Wilcoxon test, or the one-way ANOVA, depending on the distribution of residuals, to determine whether samples originate from the same distribution

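### Six psychometric variables are co-equal primaries in a trial sized for one comparison, and no rule says which result, or how many, would show that the therapy works

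*Protocol article*

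**What the plan says.** **Primary variables.** The psychological-assessment paragraph of Metrics introduces "a list of the primary variables that directly measure the impact of the therapy". The Summary of primary variables then gives CACIA delay of gratification (RR), CACIA criterial self-control (CSC), and two T-scores (Aggressive behavior, Externalizing problems), each reported by parents on the CBCL and by the youth on the YSR. That makes six psychometric variables, or four if parent and youth reports are merged. The same summary adds HR, HRV (RMSSD) and SCL.

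**The wider battery.** The same Metrics paragraph says: "These tests contain 40 variables that will help assess the effect of the therapy".

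**Sample size.** Participants derives the number by "analyzing the differences of the means according to a Student’s t". Alpha is 0.05, the target power is 80%, and d is set at 0.5. The result is 62 participants, raised to 70 for dropout. This is one comparison, with no division of alpha.

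**Efficacy analysis.** The section on assessment of cognitive therapy with biofeedback compares pre-post differences between arms by Mann-Whitney-Wilcoxon or one-way ANOVA. It lists its instruments thus: "At the beginning adolescents will fill in the CACIA, Stroop, WCST and CBCL tests". The YSR is not named there, although Block 3 (end of S9), Metrics and the Summary all include it.

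**Physiological analysis.** The two later Analysis sections compare features before and during an outburst, and at home and in the clinic. Neither describes a comparison between arms.

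**The concern.** The main goal is to verify efficacy, and the protocol gives six variables equal standing for that purpose. It puts them in no order, divides no alpha among them, and does not say whether one significant result is enough or all are needed. A mixed outcome, such as a difference on the youth-rated Externalizing score and on nothing else, could then be reported as success or as failure with equal support from the protocol. If biofeedback adds nothing, six chances at a nominal 5% level give an overall error rate well above 5%. The claim could also rest on whichever variable happened to cross the line.

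Two gaps in the list make this worse. Three variables carry the label primary with no test that could bear on the difference between arms. One primary source, the YSR, is missing from the section that defines the efficacy test.

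**Working it through.** **Inputs from the protocol article.** Alpha 0.05 (sidedness not stated), power 0.80, d = 0.5, 62 evaluable participants in equal arms (31 each) and 70 with dropout (35 each): Participants. Six psychometric primaries, four if CBCL and YSR are merged: Summary of primary variables.

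**Inputs assumed.** Each variable is tested at two-sided 0.05, because no other level is given. Any one significant result may support efficacy, because no rule is given. The correlation between outcomes is not in the document, so a range is shown.

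**1. The plan's own figure.** For two means, n per arm = 2(z₀.₉₇₅ + z₀.₈₀)²/d² = 2(1.960 + 0.842)²/0.25 ≈ 62.8. That is 63 per arm, or 64 with the t distribution, for 126 to 128 in total. The stated total of 62 does not reproduce; it is close to the per-arm number. This is a separate fault, but it bears on the cost of any fix. The calculation also confirms that only one comparison at the full 0.05 was allowed for.

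**2. Error rate with independent outcomes.** P(at least one false positive) = 1 − 0.95ᵏ.
- k = 6: 1 − 0.7351 = 26.5%
- k = 4: 1 − 0.8145 = 18.5%

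**3. Error rate with correlated outcomes, k = 6.** Simulated standard normal statistics with common correlation ρ (400,000 draws), rejecting when |Z| > 1.96 on any of the six:

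| Assumed ρ | At least one false positive |
|---|---|
| 0 | 26.5% |
| 0.3 | 24.2% |
| 0.5 | 20.6% |
| 0.7 | 16.5% |
| 0.9 | 10.8% |

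These rates count a difference in either direction, to be set against two-sided 5%. Counting only results that favour biofeedback, the independent case is 1 − 0.975⁶ = 14.1% against 2.5%.

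**4. The opposite rule.** If all six had to be significant, the same simulation gives a false-positive rate of 0.05% at ρ = 0.5 and 1.5% at ρ = 0.9. The inflation therefore depends on the success rule, which is what the protocol omits.

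**5. Power at the planned size (noncentral t, d = 0.5, two-sided).** With 31 per arm the noncentrality is 0.5 × √15.5 = 1.97.

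| Level per variable | Power, 31 per arm | Power, 35 per arm | Per arm for 80% |
|---|---|---|---|
| 0.05 (one primary) | 49% | 54% | 64 |
| 0.05/6 = 0.0083 (Bonferroni over six) | 23% | 27% | 99 |

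**The case against.** **Larger figures that a reader might infer.** Counting HR, RMSSD and SCL gives nine primaries and 1 − 0.95⁹ = 37%. Counting all 40 scores gives 1 − 0.95⁴⁰ = 87%. The document supports neither as the error rate of the efficacy claim. The three physiological variables have only within-person tests, which serve the aims that the Introduction sets apart from the main goal. The 40 scores are already separated in Metrics from the shorter primary list, so two tiers exist; what is missing is an order within the upper one.

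**The level per test.** A reader might also take it as stated that every variable is tested at 0.05. It is not: 0.05 appears only in the sample-size text.

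**Independence is unrealistic.** This stands. The Summary defines Externalizing as including aggression, and parent and youth rate the same child. The true rate is probably below 26%, but it still exceeds 5% at every correlation tried.

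**The lists may not really conflict.** The abstract's wording, "The CACIA, the Stroop, and other pre- and post-experimental tests", is open-ended and contradicts nothing. For the YSR, Block 1 presents it as the youth's version of the CBCL, so its absence from the efficacy section may be shorthand. That is plausible, but a section that defines the deciding test should name every primary source. Read literally, it covers four primaries, at 18.5% if independent.

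**Correction methods belong in an analysis plan.** That is fair, and the missing correction alone would be no finding. Declaring several co-equal primaries beside a sample size for one comparison is done in the protocol itself. A later plan would have to choose among them.

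**Conclusion.** The point holds for the six psychometric primaries. The protocol fixes its primary endpoint badly: it names several of equal rank, sizes for one, and states no rule for success. If any one significant result at 0.05 may support efficacy, the false-positive rate is about 26% with independent outcomes, and about 24%, 21%, 17% and 11% at assumed correlations of 0.3, 0.5, 0.7 and 0.9. If CBCL and YSR are merged, the independent figure is 18.5%. These sizes rest on the inferred 0.05 per variable, on the any-one-suffices reading and on assumed correlations. The absence of a success rule rests on none of them. The status of HR, RMSSD and SCL and the omission of the YSR are inconsistencies to be settled in the same edit; they do not enlarge the error rate.

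**What to change.** Before any between-arm comparison is made:

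1. Name one primary endpoint for the efficacy claim and test it at two-sided 0.05. Change in CBCL Aggressive behavior from S0 to S9 is one example; the sponsor may choose another listed variable. In choosing, note that parents take part in the evoking sessions and no blinding of parents is described, which bears on a parent-rated score.
2. Make the other five psychometric variables secondary with Holm correction (smallest p-value against 0.05/5 = 0.01, the next against 0.05/4 = 0.0125, and so on).
3. Label HR, RMSSD, SCL and the remaining test scores exploratory.
4. Use the same set, with the YSR named, in the Summary of primary variables and in the efficacy analysis.

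The cost is mainly wording, and results on the other variables become supportive only. A single primary is the least expensive route in power: Bonferroni over six would leave 23% at 31 per arm. It does not rescue the sample size, because one primary at d = 0.5 has only about 49% power at 31 per arm, or 54% if all 35 per arm are evaluable. The stated 80% power therefore needs its own correction.
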